## Abstract

**Background:** Preterm birth is associated with most cases of neonatal deaths and negative health outcomes, and hypertensive disorders. Hypertension is influenced by maternal behavior, such as physical activity. Physical activity is associated with better outcomes for mother and fetus, besides healthier weight gains during pregnancy. Few women are physically active during pregnancy and few clinical trials have been carried out with pregnant women. The aim of this paper is to describe the protocol of a controlled trial evaluating whether regular exercise during pregnancy may result in improved maternal-child health and neonatal outcomes.

**Methods/Design:** The PAMELA (Physical Activity for Mothers Enrolled in Longitudinal Analysis) trial is a randomized controlled trial nested in a birth cohort study. Eligible women belonging to the birth cohort will be invited (between the 16th and 20th week of gestation) to enroll in the trial. Baseline data (blood and urine samples, anthropometry and pulmonary function) will be collected at enrollment. The same assessments will be repeated eight and 16 weeks after baseline. After randomization, women will be allocated into either one of these groups: control, 426 women who will be advised to keep their usual daily activities; and intervention, 213 women who will engage in an exercise program, three sessions a week. At least 70 % attendance over 16 weeks will be required to be considered compliant to the intervention. Exercise protocol will include aerobics, strength and flexibility training. Maternal and child outcomes will be measured at the 36th week of gestation, at birth and at three, 12, 24 and 48 months postpartum. An intention-to-treat analysis will be performed.

**Discussion:** Few women are active during pregnancy and a vast majority decrease their activities or even quit exercising. We present a population-based regular exercise intervention focused on the prevention of hypertension, pre-eclampsia and preterm birth. Data on the underlying cohort will allow future analysis using different outcomes with low probability of recall bias or misclassification of exposure status. Results will potentially influence prenatal care counseling in regards to physical activity.

**Trial registration:** Clinicaltrials.gov identifier: NCT02148965, registered on 22 May 2014.

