### Primary outcome measures

Preterm birth (gestational age below 37 weeks of pregnancy), and pre-eclampsia (blood pressures above 140/90 mmHg and proteinuria above 15.0 mg/dL) will be assessed during pregnancy and soon after birth.

[figure not shown]

**Fig. 1** Study design

**Table 1** Exclusion criteria of the randomized controlled trial

| Exclusion criteria            | Description                                                   |
|-------------------------------|---------------------------------------------------------------|
| Age                           | Below 18 years                                                |
| Hypertension                  | Diagnosed before pregnancy/Self-reported                      |
| Diabetes                      | Diagnosed before pregnancy/Self-reported                      |
| Preterm birth                 | History of previous preterm birth                             |
| Miscarriage                   | History of previous miscarriage                               |
| Heart disease                 | Diagnosed before pregnancy/Self-reported                      |
| In vitro fertilization | Fertilization in the current pregnancy                        |
| Double/twin pregnancy         | Twin pregnancies confirmed by ultrasound                      |
| Persistent bleeding           | Women presenting persistent bleeding                          |
| Severe obesity                | Body mass index above 35 kg/m                     |
| Heavy smokers                 | Smoking more than 20 cigarettes a day                         |
| Active women                  | Weekly leisure-time physical activity > 150 min/Self-reported |

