### Sample size calculation

For the sample size calculation, based on a statistical power of 80 %, a level of significance set at 5 % and using different outcomes from the last birth cohort [28] and estimates based on secular trends (preterm birth at 16 %, gestational hypertension at 18 %, leisure-time physical activity during pregnancy at 13 % and estimate of risk reduction with the intervention at 30 %), we estimated that 213 women would be necessary for the intervention group. The intervention:control ratio will be 1:2, therefore 426 will be included as the control group.

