### Statistical analysis

Statistical analyses will be conducted on an intention-to-treat basis, but secondary analyses will be performed, including only those considered adherent to the protocol. Baseline characteristics will be presented using descriptive statistics to compare both groups.

According to the type and distribution of variables, between-groups differences will be evaluated using adequate tests. Continuous variables will be analyzed by t tests (for symmetrically distributed data), or Mann-Whitney U tests (for asymmetrical data). Categorical

[figure not shown]

**Table 2** Stages of training routines during pregnancy according to week of intervention

| Weeks of intervention | Warm-up | Aerobic exercise | Strength training/Floor exercises | Stretching |
|-----------------------|---------|------------------|-----------------------------------|------------|
| 1 to 4, Stage 1       | 5 min   | 15 min           | 35 min (sets: 3 × 12 repetitions) | 5 min      |
| 5 to 10, Stage 2      | 5 min   | 20 min           | 30 min (sets: 3 × 10 repetitions) | 5 min      |
| 11 to end, Stage 3    | 5 min   | 25 min           | 25 min (sets: 3 × 8 repetitions)  | 5 min      |

variables will be analyzed with chi-square tests or Fisher's exact test, as appropriate. General linear model or logistic regression will be employed to control for confounding factors. More specifically, based on the perinatal study information, preterm birth, gestational diabetes and eclampsia incidences will be compared in the two groups using chi-square tests, followed by multivariable analyses when adequate; linear regressions will be carried out to evaluate potential differences in birth weight, gestational weight gain and lipid profile. Analysis will be carried out in the statistical package STATA 12.0 (StataCorp, [name]) and significance will be set at 5 %.

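### The primary outcome pre-eclampsia has no planning rate and no test that names it: the sample size uses gestational hypertension and the analysis section names eclampsia.

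*Protocol*

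**What the plan says.** Three sections of the Protocol bear on the hypertensive primary outcome, and each names a different condition.

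- **Primary outcome measures** lists two outcomes: "Preterm birth (gestational age below 37 weeks of pregnancy), and pre-eclampsia (blood pressures above 140/90 mmHg and proteinuria above 15.0 mg/dL". Both are to be assessed in pregnancy and shortly after birth.
- **Sample size calculation** is "based on a statistical power of 80 %, a level of significance set at 5" %. Its inputs are "preterm birth at 16 %, gestational hypertension at 18 %, leisure-time physical activity during pregnancy at 13" %, with an "estimate of risk reduction with the intervention at 30" %. The result is 213 intervention and 426 control women. No pre-eclampsia rate appears.
- **Statistical analysis** gives a general rule (chi-square or Fisher's exact test for categorical variables). It then becomes more specific, for data from the perinatal study: "preterm birth, gestational diabetes and eclampsia incidences will be compared in the two groups using chi-square tests". Pre-eclampsia is not named in this section.

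Gestational hypertension and eclampsia appear neither under Primary nor under Secondary outcome measures. The Abstract describes an intervention "focused on the prevention of hypertension, pre-eclampsia and preterm birth", which names hypertension beside pre-eclampsia.

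**The concern.** A primary outcome should carry one name through its definition, its sample size and its test. Here the definition says pre-eclampsia, the planning rate belongs to gestational hypertension, and the named test belongs to eclampsia.

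Two things are at stake. First, a reader may take the single 80 % power figure to cover both primary outcomes, and then read a null result for pre-eclampsia as evidence against an effect that the trial had little chance of detecting. Second, the sentence that narrows the general test rule names a condition that is not an outcome and leaves out one that is primary. An analyst who follows it to the letter would report a comparison that nobody defined, and would reach pre-eclampsia only by default.

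**Working it through.** **1. The three names side by side**

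| Protocol section | Condition named | Listed as an outcome? |
|---|---|---|
| Primary outcome measures | pre-eclampsia (blood pressure and proteinuria) | yes, primary |
| Sample size calculation | gestational hypertension, 18 % | no |
| Statistical analysis | eclampsia | no |

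**2. Inputs**

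- From Sample size calculation: n₁ = 213 (intervention), n₂ = 426 (control), 30 % relative reduction, 5 % significance, 80 % power, control rates 16 % (preterm birth) and 18 % (gestational hypertension).
- Assumed: a two-sided test, because sidedness is not stated; and pre-eclampsia control rates of 3 to 10 %, because no rate is given.

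**3. Formulas** (two proportions, pooled variance under the null, no continuity correction)

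With p₂ the control risk, p₁ = 0.7·p₂, d = p₂ − p₁ and p̄ = (213·p₁ + 426·p₂)/639:

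- s₀ = √[p̄(1 − p̄)(1/213 + 1/426)]
- s₁ = √[p₁(1 − p₁)/213 + p₂(1 − p₂)/426]
- power = Φ[(d − 1.96·s₀)/s₁]

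The number needed in the intervention arm at 1:2 is n₁ = {1.96·√[1.5·p̄(1 − p̄)] + 0.842·√[p₁(1 − p₁) + p₂(1 − p₂)/2]}²/d².

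**4. The plan's own figure**

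- Preterm birth, 16 % to 11.2 %: 611 in the intervention arm (480 one-sided). Power with 213:426 is 36 %.
- Gestational hypertension, 18 % to 12.6 %: 532 (418 one-sided). Power with 213:426 is 41 %.

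For the second: d = 0.054, p̄ = 0.162, s₀ = 0.0309, s₁ = 0.0294. Then (0.054 − 1.96 × 0.0309)/0.0294 ≈ −0.22, and Φ(−0.22) ≈ 0.41.

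Continuity correction raises the numbers needed (642 and 560). Unpooled variance gives 568 and 496 two-sided, and 448 and 390 one-sided. None of these is close to 213. This shortfall exists whatever the hypertensive outcome is called, so it is a separate defect.

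**5. Power for pre-eclampsia at assumed control rates** (213:426, 30 % reduction, two-sided 5 %)

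| Assumed control rate | Expected events, control / intervention | Power | Intervention n for 80 % |
|---|---|---|---|
| 10 % | 43 / 15 | 23 % | 1038 |
| 8 % | 34 / 12 | 18 % | 1322 |
| 5 % | 21 / 7 | 12 % | 2175 |
| 3 % | 13 / 4 | 8 % | 3691 |

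At 5 %: d = 0.015, p̄ = 0.045, s₀ = 0.0174, s₁ = 0.0164. Then (0.015 − 1.96 × 0.0174)/0.0164 ≈ −1.16, and Φ(−1.16) ≈ 0.12.

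**6. Splitting the shortfall**

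The drop from 80 % to 41 % at the 18 % planning rate belongs to the sample size arithmetic. Only a further drop below 41 % comes from planning on a different condition, and its size depends on the assumed rate.

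**The case against.** The strongest reply is that this is loose wording around an outcome that is properly defined. Much of that stands.

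- **The endpoint is fixed.** Primary outcome measures names pre-eclampsia with numeric thresholds. A reader might infer that the hypertensive primary is open and could be chosen after the data are seen. One stray word in the analysis section and one planning input do not override a defined primary outcome.
- **A test exists.** A reader might infer that pre-eclampsia has no planned comparison. It is a yes/no variable, so the general chi-square or Fisher rule covers it. The sentence naming eclampsia is also confined to perinatal-study information and does not claim to list every primary test. What is missing is a test that names the outcome.
- **The subset argument is not proven.** The definition requires raised blood pressure and proteinuria, which suggests a rate below 18 %. But the protocol does not define the gestational hypertension category behind the 18 %. If that category leaves out cases with proteinuria, pre-eclampsia is not a subset of it. A lower rate is plausible but cannot be shown from the document.
- **No 80 % claim is made for pre-eclampsia by name.** The protocol gives one power figure from several inputs. The valid criticism is that this figure cannot be carried over to pre-eclampsia.
- **Eclampsia may be a slip for pre-eclampsia.** That is likely enough, but the text does not say so, and correcting the slip would leave the planning rate unaddressed.

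A statistical analysis plan could settle the test, but the mismatch lies between sections of the protocol itself.

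**Conclusion.** The point holds as an inconsistency between a defined primary outcome and the two sections that should serve it. Pre-eclampsia is primary, no rate for it enters the sample size, and the specific analysis sentence names a condition that is not an outcome. The 80 % power cannot be attributed to pre-eclampsia.

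The size rests on assumptions. With 213:426, a 30 % relative reduction and a two-sided 5 % pooled test, power is 8 to 23 % for control rates of 3 to 10 %, none of which comes from the protocol. If pre-eclampsia were as frequent as the 18 % used for gestational hypertension, power would still be only 41 %. So the conclusion that power is well below 80 % does not depend on pre-eclampsia being rarer than 18 %; only the extra loss does. The loss from 80 % to 41 % should not be charged to the naming problem.

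**What to change.** 1. In Statistical analysis, replace eclampsia with pre-eclampsia as defined under Primary outcome measures.
2. In Sample size calculation, state an assumed control incidence for pre-eclampsia on that definition, with its source, and the power that 213:426 gives for it. Failing that, state that 80 % power is not claimed for pre-eclampsia.

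Pre-eclampsia should remain the primary outcome. Making gestational hypertension primary so that the endpoint matches the 18 % is not recommended: it would change a primary outcome while, according to Trial status, recruitment is ongoing.

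The cost is one corrected word and one restated or withdrawn power statement, which will be less favourable than the present one. No data collection or visit changes. The failure of 213 to follow from the stated inputs needs its own correction and is not cured by these edits.

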### Logistics and setting

The study begins with one initial contact with the mother, prior to the 16th week of gestation, when interviewers ask for contact information, conduct a brief interview and hand a leaflet explaining the controlled trial. After enrollment in the study, women will be invited to go to the Epidemiology Research Center to collect baseline data, that is, blood and urine sampling, anthropometry, blood pressure and lung function. The same assessments (in both groups) will be repeated at eight and 16 weeks

after baseline. The facilities of the Federal University of Pelotas at the Physical Education School will be used for the intervention. A second interview at hospital will take place soon after birth (when children will be measured and mothers will be asked about many aspects of their pregnancy). After these initial data collections, when children are three, 12, 24 and 48 months, interviews will be carried out at the Epidemiologic Research Center or the participant's household. Fig. 2 shows the recruitment flowchart and subsequent data collections.

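### The lead test for the pre-eclampsia outcome ignores baseline blood pressure and leaves adjustment undefined; fixing that covariate in advance gains a modest, assumption-dependent amount of power at almost no cost

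*Protocol*

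**What the plan says.** Three places in the Protocol bear on this.

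- **Primary outcome measures.** One of the two primary outcomes is "pre-eclampsia (blood pressures above 140/90 mmHg and proteinuria above 15.0 mg/dL").
- **Logistics and setting.** After enrolment, women attend the research centre to "collect baseline data, that is, blood and urine sampling, anthropometry, blood pressure and lung function". The same assessments are repeated in both groups at eight and 16 weeks.
- **Statistical analysis.** For preterm birth, gestational diabetes and eclampsia, the "incidences will be compared in the two groups using chi-square tests, followed by multivariable analyses when adequate". A general sentence before it says that a general linear model or logistic regression will serve to control for confounding. No covariate is named, and nothing says what would make a multivariable analysis adequate.

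The Sample size calculation gives the only event rates: "preterm birth at 16 %, gestational hypertension at 18" %. It gives no rate for pre-eclampsia. No section gives a correlation, R² or odds ratio linking baseline blood pressure to any outcome.

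**The concern.** The comparison is fixed as a test that uses only group and outcome, while a measurement that plausibly predicts the outcome is taken before exercise begins. Two things are at stake.

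**Precision.** In a randomised trial the main reason to adjust for a baseline variable is to sharpen the comparison. The Protocol gives confounding as its reason, although its Background section says that random allocation will balance potential confounders. Read that way, adjustment looks optional, and precision is never considered.

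**An open choice.** With no criterion and no covariate, the decision to fit a multivariable model, and what goes into it, can be made after the crude result is known. A primary outcome then has two possible answers. This part of the concern needs no numerical assumption.

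**Working it through.** **Inputs from the Protocol (Sample size calculation).** The calculation is "based on a statistical power of 80 %, a level of significance set at 5" %; control rates are "preterm birth at 16 %, gestational hypertension at 18 %, leisure-time physical activity during pregnancy at 13" %; the effect is "estimate of risk reduction with the intervention at 30" %; and "we estimated that 213 women would be necessary for the intervention group", with 426 controls (1:2). I take the 5 % as two-sided, because the Protocol does not say.

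**Assumed, because the Protocol gives no figure.** The pre-eclampsia rate (18 % borrowed from gestational hypertension, then 10 % and 5 %) and the correlation between baseline pressure and a latent normal outcome (0.3 to 0.6).

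**Step 1: the plan's own figure.** Take p₀ = 0.18, p₁ = 0.7 × 0.18 = 0.126, k = 2 controls per intervention woman, and pooled p̄ = (0.126 + 2 × 0.18)/3 = 0.162.

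n₁ = [1.96 √((1 + 1/k) p̄(1 − p̄)) + 0.8416 √(p₁(1 − p₁) + p₀(1 − p₀)/k)]² / (p₀ − p₁)²

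= [1.96 √(1.5 × 0.1358) + 0.8416 √(0.1101 + 0.0738)]² / 0.054²

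= (0.8845 + 0.3609)² / 0.002916 ≈ 532.

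The stated 213 is not reproduced. Starting from 16 %, the same formula gives 611. One-sided tests give 418 and 480.

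**Step 2: power of the chi-square at 213 versus 426.**

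- SE under the null = √(0.162 × 0.838 × (1/213 + 1/426)) = 0.0309
- SE under the alternative = √(0.126 × 0.874/213 + 0.18 × 0.82/426) = 0.0294
- Power = Φ((0.054 − 1.96 × 0.0309)/0.0294) ≈ 41 %

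At 16 % versus 11.2 % it is 36 %.

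**Step 3: what the covariate adds.** Trials of 213 versus 426 were simulated, 4,000 per cell. The outcome is a latent normal variable, correlated with a baseline value and cut at arm-specific thresholds that give the stated risks. Monte Carlo error is about 0.8 points per power figure at 18 %, and smaller at lower rates. Moving from a Pearson chi-square to a likelihood-ratio (LR) test changes power even without a covariate, so the fair comparison is LR without against LR with baseline pressure.

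| Risks | Correlation | LR without | LR with | Gain from covariate |
|---|---|---|---|---|
| 18 % vs 12.6 % | 0.3 | 44.6 % | 46.0 % | 1.4 |
| 18 % vs 12.6 % | 0.5 | 42.9 % | 47.5 % | 4.6 |
| 10 % vs 7 % | 0.5 | 26.0 % | 28.4 % | 2.4 |
| 5 % vs 3.5 % | 0.5 | 15.2 % | 15.4 % | 0.2 |

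In the cell at 18 % and 0.5, Pearson gives 41.3 %. The whole step to adjusted LR is therefore 47.5 − 41.3 = 6.2 points, of which 42.9 − 41.3 = 1.6 is only the change of test. At correlation 0.6, Pearson gives 41.0 % and adjusted LR 50.7 %; taking off the same 1.6 points leaves 9.7 − 1.6 ≈ 8. Repeat runs put the gain at about 3.5 points for 10 % and about 1 point for 5 %.

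**Step 4: a second parametrisation.** Prognostic strength is set as an odds ratio (OR) per SD of baseline value, and the adjusted Wald test is compared with Pearson (6,000 trials per cell). At 18 % the gain is about 0 at OR 1.35, 1.8 points at 2.0, 4.1 at 2.7, 6.6 at 3.7 and 10.0 at 5.0. At 5 % the Wald test loses 0.6 to 2.4 points. The latent-normal model agrees: at 5 % and correlation 0.5, adjusted Wald power is 11.0 % against 12.8 % for Pearson. The choice of test therefore matters when events are few.

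**Step 5: type I error.** Under the null at 18 % and correlation 0.5, 10,000 trials gave 5.3 % for both Pearson and adjusted LR; a run of 4,000 gave 5.4 % and 5.9 %.

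**The case against.** The strongest reply has four parts.

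1. **The chi-square is valid.** It holds its level in a randomised comparison of a binary outcome, and preferring an adjusted model is a matter of efficiency. This stands: the point is a better method, not an error in the test.
2. **Covariates belong in the SAP.** A SAP may exist and may define the model. This stands for the covariate list. It does not cover what the Protocol itself fixes: an unadjusted lead test, with adjustment conditional on a judgement it does not define.
3. **The sentence says eclampsia.** Reading it as pre-eclampsia is an inference. It is a likely one, because the term stands beside preterm birth, the other primary outcome, and no other analysis sentence names pre-eclampsia.
4. **The covariate may be weak.** Table 1 excludes women with hypertension diagnosed before pregnancy and those with a body mass index above 35 kg/m², which plausibly narrows the range of baseline pressure. Pre-eclampsia also needs proteinuria, so its rate may be well below 18 %. Both stand, and both push the gain towards the low end of the range.

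A reader might infer from the simulations that the plan's own inputs imply a loss of 6 to 7 points. They do not. The correlation of 0.5 is not in the Protocol, the 18 % is for gestational hypertension, and part of that difference is the change of test. A reader might also infer that baseline pressure is the best predictor the trial holds, but no section ranks predictors.

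**Conclusion.** The point holds as a modest improvement with an uncertain yield. The Protocol makes an unadjusted test the lead comparison for what appears to be the pre-eclampsia outcome and leaves adjustment undefined, although a relevant baseline measurement is already planned in both arms.

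Like for like, fixing baseline blood pressure as a covariate adds roughly 1 to 8 points of power at 18 % versus 12.6 % for assumed correlations of 0.3 to 0.6. At a correlation of 0.5 that is about 5 points, falling to about 2 to 4 at a 10 % rate and close to none at 5 %. Every one of these figures rests on an assumed correlation and an assumed pre-eclampsia rate.

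It would be wrong to conclude that adjustment rescues the trial's power. At 18 % the design delivers about 41 % against a stated 80 %, and a few points do not close that gap. Closing the choice between crude and adjusted results is worth having even where the power gain is negligible.

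**What to change.** In the Statistical analysis section:

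- Name pre-eclampsia explicitly, in place of eclampsia if that is what is meant.
- Make its primary analysis a logistic regression on randomised group plus continuous baseline blood pressure, fixed in advance.
- Use a likelihood-ratio or score test rather than Wald, because events may be few.
- Report a standardised risk difference or risk ratio from the model, so that the effect stays on the risk scale used for planning.
- Keep the chi-square as a supporting crude comparison, and delete the *when adequate* condition for this outcome.
- Give precision, not confounding, as the reason for adjusting.

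The cost is wording only, since the measurement is already planned. Three small downsides remain. The model's odds ratio is conditional, which the standardised estimate resolves. A few missing baseline values would need simple imputation. If events are rare, the power gain will be slight.

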### Secondary outcome measures

Secondary outcomes will be assessed during pregnancy and until children reach the age of 48 months, specifically: blood lipid profile, lung function (peak expiratory flow - nSpire Health PiKo-1® - nSpire Health, Inc. - [name]), gestational diabetes (self-reported, by the time of delivery), gestational weight gain (calculated based on pre-gestational weight and weight at admission to deliver), mode of delivery (vaginal or cesarean section), birth weight (in grams), length at birth (in cm) and fetal growth (according to the new Intergrowth-21st fetal growth curves [26]). At three months post-partum two outcomes will be measured: post-partum weight retention (difference between current weight and pre-gestational weight) and depression (measured by the Edinburgh Postnatal Depression Scale). Infant neurodevelopment will be assessed (measured by the Battelle Developmental Inventory) at the 12, 24 and 48-month visits [27].

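### Peak expiratory flow and lipids: the stated analysis does not use the baseline value, which costs precision in these secondary outcomes but not validity

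*Protocol*

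**What the plan says.** Protocol, Logistics and setting: after enrolment, women attend the research centre to "collect baseline data, that is, blood and urine sampling, anthropometry, blood pressure and lung function". The section continues: "The same assessments (in both groups) will be repeated at eight and 16 weeks" after that visit. Protocol, Secondary outcome measures, lists blood lipid profile and lung function (peak expiratory flow), so both belong to assessments made three times.

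Protocol, Statistical analysis, makes four statements that bear on these outcomes:

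- The general rule: "Continuous variables will be analyzed by t tests (for symmetrically distributed data), or Mann-Whitney U tests (for asymmetrical data").
- The purpose of regression: "General linear model or logistic regression will be employed to control for confounding factors".
- The method for three named outcomes: "linear regressions will be carried out to evaluate potential differences in birth weight, gestational weight gain and lipid profile".
- The only stated use of baseline data: "Baseline characteristics will be presented using descriptive statistics to compare both groups".

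Peak expiratory flow is not among the three named outcomes, so the general rule applies to it. Lipid profile is among them, but the covariates of its regression are not given.

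**The concern.** In a randomised trial, allocation deals with confounding. The reason to put an outcome's baseline value into the model is different: it removes variation between women that was there before treatment, and it corrects for chance imbalance in that value. The Protocol collects the baseline values but gives regression only the task of confounding control, and gives baseline data only a descriptive role.

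For peak expiratory flow the matter goes beyond an omitted covariate list. A two-sample t test or Mann-Whitney test has no place for a covariate, so the stated method excludes the adjustment. The rule also lets the shape of the data decide whether the comparison is of means or of ranks.

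At stake is the width of the confidence intervals for these secondary outcomes. The primary outcomes, preterm birth and pre-eclampsia, are binary and are not affected.

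**Working it through.** **The plan's own figure.** The Protocol gives no power or detectable difference for any continuous outcome, so there is none to reproduce. The 213 and 426 women in Sample size calculation come from binary outcomes and are taken here as given.

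**Inputs from the Protocol**
- 213 intervention and 426 control women, 80% power, 5% significance (Sample size calculation).
- Exercise starts between weeks 16 and 20 of gestation (Intervention procedures). Repeat assessments come 8 and 16 weeks after baseline (Logistics and setting).

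**Assumptions**
- The 5% level is two-sided; the Protocol does not say.
- Every woman has follow-up data.
- The correlation r between baseline and follow-up is 0.3, 0.5 or 0.7. The Protocol gives neither a correlation nor an SD, so results are in SD units.
- Lipids are assayed in the baseline blood sample. The Protocol names blood sampling at baseline but not the assay.

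**Step 1, no baseline.** Detectable difference = (1.96 + 0.84) × √(1/213 + 1/426) = 2.80 × √0.00704 = 2.80 × 0.0839 = 0.235 SD.

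**Step 2, baseline as covariate.** ANCOVA multiplies the residual variance by 1 − r², so the detectable difference is 0.235 × √(1 − r²). The equivalent gain in sample size is 1/(1 − r²) − 1.

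| r | Variance remaining | Variance removed | Detectable difference | Equivalent extra women | Power for 0.2 SD |
|---|---|---|---|---|---|
| no adjustment | 1.00 | – | 0.235 SD | – | 66% |
| 0.3 | 0.91 | 9% | 0.224 SD | 10% | 70% |
| 0.5 | 0.75 | 25% | 0.204 SD | 33% | 79% |
| 0.7 | 0.51 | 49% | 0.168 SD | 96% | 92% |

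**Step 3, change from baseline.** The general rule does not say whether raw follow-up values or changes are tested. If changes were tested, with equal variance at both visits, the variance factor would be 2(1 − r): 1.4, 1.0 or 0.6 at the three correlations. Each exceeds the ANCOVA factor (0.91, 0.75, 0.51). Power for 0.2 SD would be 52%, 66% or 87%. At r = 0.3 a change score does worse than ignoring baseline.

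**Step 4, timing.** If baseline falls in the same 16- to 20-week window, the repeat visits fall at 16 + 8 to 20 + 8 = 24 to 28 weeks, and at 16 + 16 to 20 + 16 = 32 to 36 weeks. Women are thus compared across a four-week range of gestation at each visit, and gestational age is a natural second covariate.

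**The case against.** The strongest reply is that covariate lists usually belong in a statistical analysis plan, which is not at hand, and that silence is not exclusion. This stands in part. For lipids the Protocol plans a linear regression with its covariates left open; baseline could enter it without contradicting any sentence. For lipids the point is therefore a request to state the covariate. For peak expiratory flow the reply fails as far as the named tests go, because they cannot take a covariate. The general linear model mentioned alongside them is there for confounding.

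It is also fair that the size depends on an assumed correlation. At r = 0.3 the gain is slight (0.235 to 0.224 SD); it becomes large only towards 0.7. Incomplete follow-up would raise all the detectable differences.

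Several stronger readings are tempting, and the text does not support them:

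- A reader might infer that lipids and gestational weight gain are compared only by unadjusted tests and that baseline is never used. The regression sentence rules out the first and leaves the second open for lipids. Weight gain already uses a starting weight: "gestational weight gain (calculated based on pre-gestational weight and weight at admission to deliver").
- A reader might infer that adjustment of the continuous outcomes is left to later judgement. The conditional wording on multivariable analysis is attached to preterm birth, gestational diabetes and eclampsia. The linear regressions are stated without condition.
- A reader might extend the point to blood pressure and fasting glucose. Neither is listed as a continuous outcome in Secondary outcome measures. Blood pressure serves to define pre-eclampsia, and both otherwise appear in Aim as data to be collected.

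**Conclusion.** The point holds for two secondary outcomes. For peak expiratory flow, the stated method is an unadjusted two-sample test although a baseline measurement is available. For lipids, a regression is planned but the baseline value is not stated as a covariate.

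The consequence is lost precision. A reader might infer bias, but allocation is random and an unadjusted comparison remains valid.

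On complete follow-up of 213 and 426 women and a two-sided 5% level, the detectable difference of 0.235 SD could fall to between 0.224 and 0.168 SD for correlations from 0.3 to 0.7. That equals having 10% to 96% more women. The correlations are assumptions, so the direction is firm and the size is not.

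Gestational weight gain is a lesser, related matter. It counts gain before randomisation, which exercise cannot affect. This adds noise but no bias, and the figures above do not apply to it, because it is not an outcome regressed on its own baseline value.

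**What to change.** In Statistical analysis, replace the t test/Mann-Whitney rule for outcomes measured at baseline, namely peak expiratory flow and blood lipids, with one stated model. Either ANCOVA or a linear mixed model of the 8- and 16-week values would serve. Include treatment, the baseline value of the outcome and gestational age, with visit and treatment by visit in the mixed model. Use the log scale if an outcome is skewed, in place of a switch to a rank test. State that the baseline value is there for precision and is included whatever the observed balance.

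Optionally, add measured baseline weight and gestational age at baseline to the linear regression already planned for gestational weight gain. This leaves the definition of that outcome unchanged.

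Birth weight has no baseline value and needs no change on this account.

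The cost is wording. The Protocol already schedules the measurements, subject to lipids being assayed in the baseline sample, and no extra women or visits are needed. The change should be made before outcome data are examined by group.
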